#### Protocol Amendments

Any modification to the protocol, an update will be submitted to the Australia New Zealand Clinical Trials Registry and Research Ethics Board, The National University of Malaysia, and related journal publications.

#### Recordkeeping and Specimen

Consent will be obtained from participants to collect saliva. Data obtained through this study will only be published under group data. No individual data will be identified. The saliva samples obtained will not be kept and discarded right after the cortisol level measurement and analysis. All participants’ data and information will be stored for this research as group data.

### Ethical Considerations

Ethical approval was obtained from the Research Ethics Board at the National University of Malaysia (UKM PPI/111/8/JEP-2021-894; January 28, 2021). Detailed information on the intervention and recruitment process is provided in the next sections.

## Results

This protocol, the informed consent and other relevant documents were reviewed and approved before the conduct of the research. Letters of extension and ethics approval were obtained from the Research Ethics Board at the National University of Malaysia. Amendments will be communicated to investigators, ethics review boards and publishing journals.

By January 2025, a total of 28 participants have been recruited into the study, comprising 14 in the intervention and 14 in the control group. Only 2 participants withdrew from the intervention group mainly due to a change in location and issues relating to data privacy and security. It is expected that participant recruitment will be completed by 30 January 2025. Preliminary analysis is ongoing, and the results suggest improvement in the investigated outcomes among participants in the intervention group across time. Final analysis will be conducted by March 2025, upon completing the data collection.

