#### Sample Size

Sample size calculation was performed using G*power 3.1 software (Heinrich-Heine-Universität Düsseldorf). By assuming a study power of 0.8, 95% CI (α=0.05), and a moderate effect size of 0.25 as recommended by Ferguson (2009), the *F*-test was selected alongside repeated measures ANOVA with in-between interaction, with 2 groups and the number of measurements. Thus, a total sample size of 36 was obtained, reflecting 18 participants per group. We considered a high drop-out rate of 50% as several individuals may be unwilling to participate given the adverse effects of ACEs and confidentiality in sharing experiences with the researchers. Therefore, the sample size was increased to 50, amounting to 25 participants per group.

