#### Participant Recruitment and Randomization

The participants for this study are Malaysian youths with ACE, particularly those visiting the Psychological Department at the National University of Malaysia Medical Centre. During the selection stage, participants will be approached by the researcher and seek their consent to participate in the study. Those providing affirmative responses will then be instructed to fill up the self-administered ACE questionnaire.

This assessment period is the screening stage to identify those that fulfil the inclusion criteria. Participants who score four or more of ACE will then be included in a pool of participants and assigned randomly to either the control group or intervention group. Random assignment procedure will be implemented by random allocation software, Research Randomiser [31], to generate numbers and assign participants to an intervention group or control group. Allocation concealment will be performed by a single blinding procedure, whereby the assessors of the outcome measures will be unaware of the specific group the participants belong to. In other words, only the investigator allocating participants to either the control or intervention group will be aware of this information while other assessors are blinded. Table 1 depicts the participant enrolment schedule, time points and assessments to be performed during the study period.

**Table 1 table1:** SPIRIT (Standard Protocol Items: Recommendations for Interventional Trials) schedule of enrolment, interventions, and assessments.

			Study period							Close-up
			Enrolment		Allocation		Postintervention		Four-week follow-up	
Timepoint			t_1_		0		t_2_		t3+4weeks	
**Enrolment**			✓							
	Screening	✓								
	Eligibility screen	✓								
	Informed consent	✓								
	Allocation			✓						

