**Assessments**										
	Brief Coping Orientation to Problem Experienced Scale - English and Malay version	✓				✓		✓		
	Ryff’s Scale of Psychological Well-being (SPWB) - English and Malay version	✓				✓		✓		
	Quality of Life –WHOQL-BREF - English and Malay Version	✓				✓		✓		
	Subjective stress – Perceived Stress scale - English & Malay version	✓				✓		✓		
	Personal Resources Questionnaire 2000 - English and Malay version	✓				✓		✓		
	Adult Resilience Measure-Revised - English and Malay version	✓				✓		✓		
	Biomarker - measure changes in salivary cortisol	✓				✓				
	Blood pressure (blood pressure measured with a sphygmomanometer	✓				✓				

Participants in the control group will receive no intervention, while those in the intervention group will receive five sessions of resilience-building intervention conducted by a trained facilitator. Hotlines, post session, and appropriate resources will be provided for those reporting distress after the intervention. Investigators will be blinded throughout the whole process of randomization and data collection as the whole process is handled by a research assistant (randomization), counsellor, and clinical psychologist (data collection). Under no circumstances will unbundling occur as a research assistant, counsellor, and clinical psychologist are briefed with the standard operating procedure to follow when an incident occurs. The flow diagram is presented in Figure 1.

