### Data Analysis

All data management and statistical analysis will be conducted using SPSS (version 26; IBM Corp). Data management will be performed by screening for missing data and checking for potential outliers. Descriptive statistics will be used to assess the data normality and to summarize the pre and postintervention scores for each group at different periods. Mean and SDs will be provided for normally distributed data, followed by mixed ANOVA with repeated measures to compare the pre and postintervention mean scores between and within the groups.

The assumptions of ANOVA include randomly collected and normally distributed data, sufficient sample size, homogeneity of variances, and absence of violation and outliers. Levene’s test will be applied to test the homogeneity of variance. Mixed ANOVA benefits RCT design as it allows testing for 2 groups across 2-time points. Mixed ANOVA analysis aims to handle response outcomes conducted on the same experimental unit at a different time or under different conditions [57]. The differential effects of the intervention components will be tested with interactions between the component and time. These analyses will model random slopes and intercepts for participants, explore the fixed effects of the condition, and test the repeated measures over time. This type of analysis is advantageous by accounting for missing values through the maximum likelihood estimation method [57]. Effect sizes will be computed based on Cohen *d*.

In addition, the intention-to-treat analysis will be applied to analyze the participants according to their assigned groups. This analysis includes all participants and ignores noncompliance, protocol deviation, and withdrawal. The intention-to-treat analysis is a complete trial strategy for the design, execution, and analysis of RCT, focusing on the consolidated standard of reporting trial guidelines. Thus, the number of participants in each assigned group will be analyzed by the intention-to-treat principle.

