#### Standard Operating Procedure to Manage Harm

Counsellors and clinical psychologists will evaluate if any of the participants feel discomfort or express interest in withdrawing from the studies. This assessment will be carried out during the break intervals between each session of the intervention and the follow-up periods post intervention. Participants will be asked verbally if they still feel comfortable and willing to proceed with the intervention. Follow-up and proper redirecting to resources will be practiced with individuals who dropped out of the study.

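### Preliminary results for the intervention arm are reported while data collection is open, against the stated investigator blinding, and the text on who allocates and who knows the arm contradicts itself

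*Protocol article*

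**What the plan says.** All references are to the protocol article.

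- **Results.** By January 2025, 28 participants had been recruited, 14 per arm, and 2 had withdrawn from the intervention arm. Recruitment was expected to end on 30 January 2025 and the final analysis to follow by March 2025, once data collection was complete. In between stands: "Preliminary analysis is ongoing, and the results suggest improvement in the investigated outcomes among participants in the intervention group across time".
- **Sample Size.** The target is 50, 25 per group.
- **Participant Recruitment and Randomization, before Table 1.** "Allocation concealment will be performed by a single blinding procedure", explained as outcome assessors not knowing the group. Then: "only the investigator allocating participants to either the control or intervention group will be aware of this information".
- **Same section, after Table 1.** "Investigators will be blinded throughout the whole process of randomization and data collection". The reason given is that a research assistant handles randomization, and a counsellor and a clinical psychologist handle data collection. It adds that unblinding (printed as 'unbundling') will not occur under any circumstances.
- **Data Analysis.** It covers mixed ANOVA, intention to treat and missing data. It describes no interim analysis, no stopping or sample-size rule, and no party with restricted access to accumulating results.

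**The concern.** Results for a named arm are known, and their favourable direction is published, while participants are still being enrolled and measured. That does not fit with investigators who remain blind until data collection ends. Someone has linked outcomes to arm, and the article does not say who, when, or on which participants.

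Two things are at stake. The first is the closing decision. The article gives a target of 50 and a calendar date, but does not say which governs if the date comes first, with 22 participants still to enrol (50 − 28). A known trend could influence that choice, and a reader of the final report could not exclude it. The second is the credibility of the blinding. If the document does not settle who holds the allocation sequence and who may know the arm, a reader cannot judge whether the next assignment was concealed or whether assessors were blind. Concealment protects the assignment before it is made; assessor blinding protects measurement afterwards. One cannot be delivered by the other.

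**Working it through.** **1. The statements side by side**

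| Question | Before Table 1 | After Table 1 | Results |
|---|---|---|---|
| Who allocates? | An investigator | A research assistant | – |
| Who knows the arm? | The allocating investigator | No investigator, through the end of data collection | Whoever runs the preliminary analysis (not named) |
| Is data collection finished? | – | – | No |

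The first two columns cannot both hold. The third conflicts with the second unless the analysis was done by someone outside the investigators and kept from them, which the article does not say.

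**2. The plan's own sample size**

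Inputs: "By assuming a study power of 0.8, 95% CI (α=0.05), and a moderate effect size of 0.25" and "repeated measures ANOVA with in-between interaction, with 2 groups and the number of measurements". The number of measurements m and the correlation ρ between them are not stated. Data Analysis speaks of two time points ("Mixed ANOVA benefits RCT design as it allows testing for 2 groups across 2-time points"), while Table 1 schedules the questionnaires at three.

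For the within-between interaction with k = 2 groups: λ = N·m·f²/(1 − ρ), df1 = (k − 1)(m − 1), df2 = (N − k)(m − 1).

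With m = 2 and ρ = 0.5 (both assumed):
- N = 34: λ = 34 × 2 × 0.0625/0.5 = 8.5, power 0.807. This is the smallest even N that reaches 0.80.
- N = 36: λ = 9.0, power 0.830.

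The stated 36 is therefore reproduced to within 2 participants, which makes these settings plausible but does not establish them.

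**3. Power if recruitment closed at 28 (f = 0.25, α = 0.05)**

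| m | ρ | λ | Power at N = 28 |
|---|---|---|---|
| 2 | 0.3 | 28 × 2 × 0.0625/0.7 = 5.00 | 0.58 |
| 2 | 0.4 | 28 × 2 × 0.0625/0.6 = 5.83 | 0.64 |
| 2 | 0.5 | 28 × 2 × 0.0625/0.5 = 7.00 | 0.72 |
| 2 | 0.6 | 28 × 2 × 0.0625/0.4 = 8.75 | 0.81 |
| 3 | 0.5 | 28 × 3 × 0.0625/0.5 = 10.50 | 0.81 |

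For comparison, N = 50 with m = 2 and ρ = 0.5 gives 0.93.

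**4. Type I error if the look could have ended the trial**

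Assume a between-arm test at 28 and another at 50, each two-sided at 0.05 (|Z| > 1.96), with all 28 contributing outcome data. The information fraction is 28/50 = 0.56, so the two statistics correlate at √0.56 = 0.748. Then P(|Z₁| > 1.96 or |Z₂| > 1.96) = 0.081. If only the 26 who had not withdrawn contribute, the fraction is 26/50 = 0.52 and the result is 0.082. A look that cannot lead to any decision leaves the error at 0.05.

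**The case against.** The strongest reply is that the document proves less than the sentence in Results suggests, and most of that reply stands.

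- A reader might infer that the sample size and endpoint have been left to the data. The article does not support this. Sample Size fixes 50, and no passage mentions stopping at 28, re-sizing or changing an outcome.
- A reader might take 8.1% as the trial's actual error rate. It is not. The reported trend is change over time within one arm; no between-arm test, p-value or option to stop is mentioned. The text also says 28 were recruited, not that 28 had outcome data.
- A reader might quote 72% power at 28 as a firm shortfall. That figure needs m = 2 and ρ = 0.5, and the article states neither. Under some plausible settings there is no shortfall against 80%.
- The analyst is not identified, and one of the two blinding statements already lets an investigator know the arms. A breach by a particular person who should have been blind is therefore not shown.
- A reader might infer that session staff collect the outcomes, because the harm procedure says "This assessment will be carried out during the break intervals between each session of the intervention". That assessment is a check on comfort and willingness to continue. It shows the same professions in both roles, not the same individuals. Nor does any passage say that whoever allocates also recruits.
- The article is condensed, so an interim analysis could be described in a fuller document. What can be said is that this article describes none.

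None of this removes the conflict between the reported look and the blinding statement, the contradiction over allocation, or the mislabelled concealment. Those are in the text itself and do not depend on an unseen plan.

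**Conclusion.** The point holds as a defect of the text and of conduct during the trial, not as proof of bias. Three things are wrong as written: results for the intervention arm are reported before data collection ends, although investigators are said to be blind throughout; two statements in one section disagree on who allocates and who knows the arm; and assessor blinding is presented as allocation concealment.

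The consequence is a risk whose size the documents do not fix. Type I error would be about 8.1% only if a between-arm test at 28 could have ended the trial and both looks were tested at 0.05. Power at 28 would be 0.58 to 0.81 for two measurements and ρ from 0.3 to 0.6, and 0.81 for three measurements and ρ = 0.5, all at f = 0.25. If recruitment reaches 50 and no decision rested on the look, neither figure applies.

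**What to change.** 1. Do no further by-arm analysis until the last 4-week follow-up is in and the data are locked.
2. In Results and in the final report, declare the look: its date, which data it used and who saw it. Leave out the direction of the result. State whether any decision on sample size, closing of recruitment or endpoint rested on it.
3. If recruitment closes below 50, state the power at the achieved size together with the assumed number of measurements and correlation.
4. Reconcile the two statements in Participant Recruitment and Randomization so that one named role holds the sequence, and say who else may know the arm. Describe how upcoming assignments are concealed separately from how assessors are blinded.
5. Describe the self-report outcomes as unblinded, since participants know whether they received sessions.

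The cost is wording and discipline over data access. The sponsor gives up early looks and part of the single-blind claim. Any change in procedure reaches only participants not yet allocated; for the 28 already enrolled, the text should record what was actually done.

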## Discussion

### Principal Findings

ACEs are relatively common, trigger substantial suffering and are well-documented as a risk factor for diverse physical and mental health conditions throughout life. While primary prevention is pertinent in reducing ACE, the deleterious short and long-term consequences of ACE can be mitigated by selective prevention.

This study adopted the multisystemic approach to resilience “R2,” which recognizes the importance of rugged qualities and access to resources among individuals affected by ACEs. As discussed earlier, the multisystemic model of resilience emphasizes 2 broad aspects, encompassing personal and environmental change [37]. We considered these 2 aspects as pertinent in addressing the consequences of ACEs among young adults in Malaysia, aligning with recommendations from previous studies to approach the problem in a multidimensional manner [8,38]. This study will be the first attempt to adopt an evidence-informed intervention for resilience-building among Malaysians with ACEs. In addition, this research is among the few interventions that explicitly entail both coping strategies and creating better-resourced environments around individuals affected by ACEs.

It is anticipated that the resilience-building intervention will have moderate to strong effects by ameliorating mental health, and stress, and improving participants’ resilience and resource finding compared with those in the control group. These expected findings are consistent with the report by Chandler et al [21], whereby a resilience intervention centered around 4 main components (ie, active coping, building strength, cognitive flexibility, and social support) was effective in mitigating the adverse effects of ACEs.

Our intervention is structured into 5 sessions, focusing on self-exploration and social support, coping techniques and coping skills, resource finding, spirituality, and resilience-building. These components are expected to enhance participants’ internal capacities such as self-regulation and problem-solving, thereby harnessing opportunities to achieve success in life [39]. By educating them on how to identify and gain better access to external resources, they will be motivated to accomplish life tasks and be more optimistic [42]. These events will assist in building resilience, facilitating participants’ interaction with the world around them, and using available resources effectively regardless of being exposed to adversities.

This intervention aims to focus on vital resilience components which are emotion regulation, active coping and goal setting, cognitive flexibility, physical health, mindfulness-based stress reduction, social support, self-exploration, resources and navigation, financial planning, and spirituality and religion. One of the weaknesses of this intervention is that these components will be monitored by informal assessment such as observation, tracking, and recap to ensure participants have learned and acquired the tools and knowledge. It is also difficult to ensure participants from the control group will not receive any form of therapy during the whole duration of the intervention. Hence, the therapist has to check in with the group from time to time to ensure their well-being is taken care of. If needed, the therapist will conduct a post-group counselling session with an individual who is distressed by the intervention. Given that the participants were selected from a pool of individuals obtaining a specific level of ACEs, the findings might not be generalized to the entire population of people with ACEs in the country.

### Conclusion

This is the first full clinical trial study investigating resilience-building intervention for youths with ACEs in Malaysia. There are limited studies evaluating the effectiveness of resilience-building interventions combining mental health and physiological responses as outcome measures in Malaysia. Thus, this study conceptualizes resilience from a biopsychosocial-ecological perspective and adapts resilience-building intervention in the Malaysian context. This study aims to develop resilience-building intervention modules specifically for Malaysia, focusing on the process of adapting the modules and modifications according to the Malaysian culture. This will be one of the first studies to provide evidence in the context of RCTs for resilience-building intervention combining self-report and physiological measures (ie, saliva and heart blood pressure) among individuals with ACEs. The findings will assist relevant authorities in the health and policy sectors to develop effective strategies for addressing the negative impacts of ACEs on the vulnerable population in Malaysia.

## Abbreviations

ACE: adverse childhood experience
ACE-Q: Adverse Childhood Experience Questionnaire
CBT: cognitive behavioral therapy
COPE: Brief Coping Orientation to Problems Experienced Scale
HRB: high-risk behavior
PHQ-9: Patient Health Questionnaire-9
PSS-10: Perceived Stress Scale-10
RCT: randomized controlled trial
SPWB: Ryff’s Scale of Psychological Well-being
WA-PR: Work Ability-Personal Radar
WHOQL-BREF: World Health Organization Quality of Life Assessment
